## Abstract

Anhedonia is a hallmark symptom of depression that often lacks adequate interventions. The translational gap remains in clinical treatments based on neural substrates of anhedonia. Our pilot study found that depressed individuals depended less on goal-directed (GD) reward learning (RL), with reduced reward prediction error (RPE) BOLD signal. Previous studies have found that anhedonia is related to abnormal activities and/or functional connectivities of the central executive network (CEN) and salience network (SN), both of which belong to the goal-directed system. In addition, it was found that real-time functional magnetic resonance imaging (rt-fMRI) neurofeedback (NF) could improve the balance between CEN and SN in healthy individuals. Therefore, we speculate that rt-fMRI NF of the CEN and SN associated with the GD system may improve depressive and/or anhedonic symptoms. Therefore, this study (1) will examine individuals with anhedonic depression using GD-RL behavioral task, combined with functional magnetic resonance imaging and computational modeling to explore the role of CEN/SN deficits in anhedonic depression; and (2) will utilize network-based rt-fMRI NF to investigate whether it is feasible to regulate the differential signals of brain CEN/SN of GD system through rt-fMRI NF to alleviate depressive and/or anhedonic symptoms. This study highlights the need to elucidate the intervention effects of rt-fMRI NF and the underlying computational network neural mechanisms.

## Introduction

Anhedonia is a transdiagnostic psychiatric symptom typical of psychiatric disorders, such as depression, posttraumatic stress disorder (PTSD), and schizophrenia according to the Diagnostic and Statistical Manual of Mental Disorders, Fifth Edition (DSM-5), and is associated with an elevated risk of suicide and chronicity of the disease (1). The biological endophenotypes of anhedonia include reduced anticipation of upcoming rewards, reduced experienced pleasure during the reward presentation, and impaired reward learning (2). Specifically, reward learning (RL) is the ability to adapt to the contingencies between action and the reward feedback, with two systems working together: The habitual system supports routine responses to deal with regular situations, while the goal-directed (GD) system is sensitive to environmental change to flexibly adapt to unfamiliar situations. The deficits in goal-directed systems play an important role across the lifespan and in various mental disorders, such as subclinical depression, trauma-related disorders, addiction, and obsessive-compulsive disorder (OCD) (3–6). Specifically, goal-directed reward learning (GD-RL) could discriminate between depressed patients and healthy controls using a machine learning algorithm (Naive Bayes) and could predict the concurrent depressive symptoms and depression traits 1 year later (7). To sum up, deficits in the goal-directed system may contribute to depression during both the symptomatic and clinical phases. However, a translational gap still remains in the clinical imaging study of the goal-directed system (8).

Neurally, the goal-directed system may involve functional interactions between the central execution network (CEN) and the salience network (SN). The CEN, including the medial frontal gyrus (MFG), superior frontal gyrus (SFG), and the anterior cingulate cortex (ACC), especially the perigenual ACC (pgACC), is essential for external, goal-directed cognitive processes (9, 10). The SN, including the anterior insula (aINS), the dorsal anterior cingulate cortex (dACC), the amygdala (AMY), the substantia nigra/ventral tegmental area (SN/VTA), ventral striatum (VS), and thalamus, is responsible for detecting salient stimuli in the environment and allocating cognitive resources to facilitate goal-directed behavior (10, 11). SN may function as a gate to detect the salience of stimuli and co-activate task-relevant networks such as CEN to facilitate goal-directed behavior (12), through the shift between default mode network (DMN) and CEN (13). Previous studies showed global circuit–phenotype associations across clinical anxiety and depression, with distinct CEN (e.g., ACC and dlPFC) and SN (e.g., aINS and AMY) circuits (14). Therefore, abnormalities in the goal-directed system, and in particular the CEN/SN decoupling, may represent distinctive neural phenotypes of depression.

On the one hand, the dysfunctional networks of CEN and SN persist during depressive episodes. We previously found that depressed patients showed impaired goal-directed behavior, accompanied impairments in CEN, such as over-activation in the left lateral PFC (LPFC), as well as SN, such as under-activation in VTA, dorsal striatum (DS), and orbital frontal cortex (OFC) (7) (Figure 1), the last of which plays a critical role in controlling the transition between goal-directed and habitual behavior (15). The neural abnormalities in VTA during habitual learning do not normalize during remission (16). Further evidence suggested that enhanced resting-state functional connectivity (RSFC) between subregions of ACC (including pgACC and sgACC) and caudate could predict future anhedonia symptoms in adolescent depression (17, 18). Specifically, neural activation to uncertain rewards in ACC during reward learning tasks could predict anhedonia symptoms 1 year later when baseline anhedonia is controlled for (19). Collectively, these studies suggest that neural impairments in the CEN and SN within the goal-directed system are not only present during the acute phase of depression but also predict the course of the disease.

**Figure 1 F1:**
[figure not shown]
Hypothesized role of goal-directed function impairments in anhedonia symptoms of depression.

On the other hand, the stress-resilience model of depression provides a framework for understanding distinct subnetworks (CEN and SN) underlying anhedonic symptoms of depression. Emerging findings from functional abnormalities of higher functional connectivity between CEN (dlPFC and pgACC) and SN (striatum and VTA) during reward-related tasks were shown in depressed patients, as well as hypo-activation in CEN (pgACC and mOFC) and SN (VS/DS) (20). Anhedonia was associated with SN overactivity in the resting state, lack of SN activation in response to positive stimuli in task-related states, and SN overactivity in response to negative stimuli (21). Stress mediates the relationship between goal-directed reward learning and anhedonia (7). Stress may contribute to impaired goal-directed processes by enhancing the connectivities between CEN and SN circuits (e.g., dlPFC and amygdala/VS) (22). The resilience to stress involves the interactions among heightened CEN (PFC) and lessened SN (mesostriatal reward circuits) neural activities (23). Taken together, goal-directed behavior depends on the adaptive redistribution of neural resources between the CEN (↓) and SN (↓), and stress may lead to an imbalance between the CEN (↓) and SN (↓), as well as aberrant connectivity during reward processing, which may contribute to anhedonia symptoms.

Neurofeedback based on real-time functional magnetic resonance imaging (rt-fMRI) uses measured changes in brain activation to help participants regulate activity in selected regions or networks. During rt-fMRI neurofeedback, participants are provided with visually presented brain network activation information in real time (24). The rt-fMRI neurofeedback targeting the brain areas within SN involved in emotion processing (e.g., amygdala, insula, and striatum) decreased the anhedonic or depressive scores (25, 26). However, the effects of rt-fMRI neurofeedback (NF) based on CEN-SN on anhedonia to the best of our knowledge have not been investigated previously. Network-based NF can be used to recalibrate the balance between brain networks (27). It has been recommended that researchers use NF methods that consider neural response across regions (i.e., functional connectivity) (28). Recent studies have found that participants can flexibly regulate the balance between the CEN and SN through rt-fMRI neurofeedback which could promote resilience to stress (29). Therefore, the use of rt-fMRI neurofeedback to improve goal-directed reward learning is a potential intervention that involves the interaction between CEN and SN. Additionally, reward learning studies have typically adopted computational modeling during behavioral tasks to estimate expected value and reward prediction errors (RPEs) (20). Therefore, the current study was designed to adopt reward learning tasks (30) and computational modeling in anhedonic individuals to examine goal-directed brain network dynamics. Network-based rt-fMRI neurofeedback will be utilized to improve the balance of CEN/SN within the goal-directed brain network (Figure 1). The within-group changes of depressive symptoms after rt-fMRI NF training of goal-directed brain network will be examined to assess the effects of rt-fMRI NF intervention to improve depressive and/or anhedonic symptoms for depressed patients. The goal-directed RL, as well as CEN/SN changes (CEN-SN functional connectivity) at 3- and 6-month follow-ups, will also be examined to evaluate the long-term rt-fMRI neurofeedback training effects. This study may provide evidence to elucidate the effect of rt-fMRI NF based on the goal-directed system in alleviating depressive/anhedonic symptoms. The rt-fMRI NF training may have clinical implications with improved safety and minor side effects (31).

## Methods and analysis

### Aim

To determine whether rt-fMRI neurofeedback of the goal-directed system could improve the depressive and/or anhedonic symptoms of depressed patients after training and at follow-ups;To examine the short-term and long-term effects of rt-rMRI neurofeedback on the goal-directed RL behavioral and/or connectivity imaging mediators.

### Participants

The study was approved by the ethical review committee at the Army Medical University (AMU, PRC) and conformed to the Declaration of Helsinki. The study has been submitted to the Chinese Clinical Trials Registry (ChiCTR, https://www.chictr.org.cn/). The trial identifier will be made available upon approval of the registration. After signing the informed consent form, the clinical data and general information of all participants will be collected, including age, gender, duration of illness, years of education, and medication history. The clinical diagnosis and symptom assessment will be completed by psychiatrists according to DSM-5 combined with a Mini-international Neuropsychiatric Interview (MINI). We will use the Hamilton Depression Scale-17 (HAMD-17) and the Montgomery–Åsberg Depression Rating Scale (MADRS) to assess anhedonia symptoms. Participant selection and recruitment processes were not conducted prior to the submission of the study.

(1) High anhedonic depression group. Inclusion criteria: ① diagnosed with major depression, with at least one core symptom (loss of pleasure or interest in all or nearly all activities) (MADRS item 8 ≥ 4) or non-reactive mood (items 1 or 2 ≥5, ② at least three following symptoms during the most severe phase of this depressive episode, including (a) significant psychomotor disturbance (HAMD items 8 or 9 ll1); (b) appetite/weight loss (HAMD items 12 or 16 = 2); (c) late insomnia (waking at least 2h earlier than usual) (HAMD item 6 ≥ 1); and (d) guilt (HAMD ≥ 1) (32); ③right-handedness. Exclusion criteria: ① comorbid with other mental disorders or drug or alcohol dependence; ② has received any previous antidepressant or antipsychotic medication (including benzodiazepines and other sedatives and hypnotics); ③ with severe physical diseases such as heart, liver, or kidney impairment, endocrine disorders, or infectious diseases; ④ substance dependence or abuse; ⑤ vision impairments; ⑥ pregnant or breastfeeding women; ⑦ MRI contraindications; and ⑧ currently receiving any emotional ability training.

(2) Healthy control group. Inclusion criteria: ① without a history of mental illness and family history of mental illness; ② age 18–55; ③ HAMD-17 < 7; and ④ right-handedness. Exclusion criteria: ① diagnosed with depression or other axis I diseases; ② has received any previous antidepressant or antipsychotic treatment (including benzodiazepines and other sedative and hypnotic drugs); ③ with severe physical diseases such as heart, liver, renal impairment, endocrine diseases, and infectious diseases; ④ substance dependence or abuse; ⑤ vision impairment; ⑥ women pregnant or breastfeeding; ⑦ MRI contraindications; and ⑧ currently receiving any emotional ability training.

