### Statistical analysis

#### Behavioral data

##### Statistical analysis

IBM SPSS Statistics 22 (https://www.ibm.com/spss) will be used. The 2 (groups: high anhedonia group and healthy control group) × 2 (transition conditions: common transition and rare transition) × 2 (reward feedback: reward and non-reward) factor mixed design will be conducted. The general linear mixed model (GLMM) will be used to investigate the main effects and interactions of the group, transition condition, and reward feedback on choice behavior. The interactions of transition conditions and reward feedback will represent the effect of the goal-directed system on the choice behavior (goal-directed RL), and the main effect of reward feedback will represent the effect of the habitual system on the choice behavior (habitual RL). The three-way interaction of the group, transition condition, and reward feedback will be examined to test for group differences in goal-directed RL. The two-way interaction of group and reward feedback will be examined to test for group differences in habitual RL.

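### The group labelled high anhedonic admits patients below the anhedonia cut-off and is contrasted only with healthy controls, so the case-control part cannot show anything specific to anhedonia

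*Protocol article*

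**What the plan says.** All references are to the protocol article.

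- **Label and entry.** Participants names a high anhedonic depression group. Its first criterion asks for major depression "with at least one core symptom (loss of pleasure or interest in all or nearly all activities) (MADRS item 8" at 4 or more), and then continues "or non-reactive mood (items 1 or 2" at 5 or more). The second criterion requires "at least three following symptoms during the most severe phase of this depressive episode", chosen from psychomotor change, loss of appetite or weight, early waking and guilt. The same section says that HAMD-17 and MADRS will be used "to assess anhedonia symptoms". It sets no SHAPS threshold.
- **Comparator.** Healthy controls must be "without a history of mental illness and family history of mental illness" and have HAMD-17 below 7.
- **Choice model.** Behavioral data, Statistical analysis, sets out a mixed design whose between-subject factor is "groups: high anhedonia group and healthy control group". The group × transition × reward interaction is the test of a group difference in goal-directed learning.
- **Imaging model.** Task-state PE signal analysis enters PE regressors with the model-based weight ω as covariate. It names no anhedonia measure.
- **Purpose of this part.** The Abstract gives the first aim as using the task, imaging and modelling "to explore the role of CEN/SN deficits in anhedonic depression". The Introduction likewise describes the task and modelling as applied to anhedonic individuals.
- **Randomised part.** Forty patients are allocated to neurofeedback (NF, 20) or yoked control (YC, 20). Intervention effect analysis compares these arms on HAMD-17 (primary) and SHAPS (secondary).

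**The concern.** Two features combine. The group name promises high anhedonia, while the criteria make the only anhedonia threshold optional. In addition, the one comparison built on that label sets depressed patients against people with no psychiatric history and a low HAMD-17, so the groups differ in depression as a whole. If the three-way interaction is found, the label invites the reader to take it as a goal-directed deficit of anhedonia. The same data would arise from a deficit common to all major depression. The interpretation of the mechanistic part is at stake, not the test of the intervention.

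**Working it through.** The protocol gives no figure for this point, so there is none to reproduce. The check is whether the criteria and models, as written, can support a statement about anhedonia.

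**Step 1: can a patient enter below the anhedonia cut-off?** Take a patient with major depression, MADRS item 8 below 4, item 1 at 5, and psychomotor change, early waking and guilt at the required levels.

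| Requirement | Met? | Anhedonia item? |
|---|---|---|
| Major depression | yes | not specifically |
| Item 8 ≥ 4, or items 1 or 2 ≥ 5 | yes, by the second route | only in the first route |
| Three of four further symptoms | yes | none of the four |
| SHAPS threshold | none set | – |

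This patient is eligible on these criteria and is labelled high anhedonic. (Items 1 and 2 are read as MADRS items because they follow the MADRS item in the same sentence. The result does not depend on this.)

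**Step 2: what does the patient-control contrast estimate?** Let D be the deficit shared by all patients with major depression, A the additional deficit that goes with anhedonia, and q the share of patients without that additional deficit. Treating A as all-or-nothing for simplicity:

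expected patient-control difference = D + (1 − q)·A

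- One quantity is estimated, and D, A and q are unknown.
- With q = 0 the difference is D + A, which still does not separate the two.
- As q rises from 0 to 1, the weight on A falls from 1 to 0, so the label fits the estimate less and less.
- With A = 0 and D not zero, the contrast still shows a difference.

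The lack of specificity thus comes from the comparator and the missing severity term. The mixed entry adds to it.

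**Step 3: does another term in these two models separate D from A?** The choice model has group, transition and reward. The imaging model has PE regressors and ω. Neither has SHAPS, MADRS item 8 or any other anhedonia score, and there is no depressed comparison group with low anhedonia.

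**Step 4: are data available that could separate them?** Pre- and post-test says the primary and secondary outcome measures are assessed in all subjects before the intervention. Baseline HAMD-17 and SHAPS therefore exist for all 40 patients.

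**Step 5: how precise would a within-patient estimate be?** For scale, take a partial correlation between baseline SHAPS and a subject-level measure such as ω, adjusted for one covariate (HAMD-17). On Fisher's z scale:

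SE = 1/√(n − 1 − 3) = 1/√36 = 0.167; 95% half-width = 1.96 × 0.167 = 0.327

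An estimate of 0 would have an interval of about −0.32 to 0.32 after back-transformation. This assumes complete data and approximate normality. It is informative about a strong association only.

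**The case against.** The strongest defence is that the formal Aim section does not ask the anhedonia-specific question. It asks whether NF improves depressive and/or anhedonic symptoms in depressed patients, and what it does to the mediators. The Abstract speaks of exploring deficits in a patient population, in what Sample size calls a feasibility study with limited resources. On that view, the absence of a depressed low-anhedonia group is a reasonable economy. The article also points to a preregistration and a checklist, not shown here, that may list further analyses. And the entry criteria cite a source that may count non-reactive mood as part of its construct.

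Much of this stands. It rules out calling the design invalid, and no extra comparison group is asked for. It does not remove the mismatch, because the label, the models and the Abstract's first aim are all stated in the article, and together they lead to a reading that the contrast cannot support.

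A reader might go further, in four ways that the protocol does not support:

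- **That patients enter through low mood alone.** They do not. The route is described as non-reactive mood and also needs major depression and three further symptoms.
- **That the patients are compared only with healthy controls throughout.** This is true of the choice model. The primary and secondary outcomes are compared between randomised NF and YC arms.
- **That the anhedonia score goes unused.** SHAPS is an outcome after training and at 3 and 6 months, and the exploratory mediation analysis relates ω and the CEN-SN activation difference to changes in depressive and/or anhedonic symptoms. What is missing is narrower: baseline SHAPS as a predictor in the choice and PE models.
- **That patients below the item 8 cut-off have no anhedonia and cannot improve on SHAPS.** Falling below one cut-off is not absence of the symptom. Neither the number of such patients nor their SHAPS scores are given, so a loss of power cannot be derived.

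**Conclusion.** The point holds for the case-control, mechanistic part. As written, that part can show that patients with depression differ from healthy people in goal-directed learning. It cannot show that the difference is specific to anhedonia, and the group name claims more than the entry criteria guarantee.

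The share of patients below the anhedonia cut-off is unknown, so no numerical bias can be attached. The lack of specificity does not depend on that share. The conclusion rests on the criteria and model terms as printed in the article.

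The randomised NF versus YC comparisons of HAMD-17 and SHAPS keep their validity. Mixed entry affects whom those results describe. This is a matter of interpretation that should be put right, not a flaw in the trial's main comparison.

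**What to change.** 1. Within the 40 patients, add baseline SHAPS as a continuous predictor to the reward × transition choice model, and read the SHAPS × reward × transition term. Enter baseline HAMD-17 with the same interactions, since a main effect alone would not adjust that term for overall severity.
2. Add baseline SHAPS, adjusted for baseline HAMD-17, to the PE-signal model in the same patients.
3. Declare both analyses exploratory and report estimates with intervals. Rest any statement specific to anhedonia on these terms, and state that a wide interval leaves the question open.
4. Describe the patient-control contrast as depression versus health wherever it is reported.
5. Reconcile the group label with the entry criteria, so that the name describes the patients who can actually enter.

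No change to recruitment or new data is needed, because both scales are already collected before training. The cost is a little extra analysis and an estimate that will be imprecise with 40 patients. Participants states that selection and recruitment had not been conducted before submission, so at that stage the analysis could still be fixed in advance.

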### Procedure

This study is a double-blind randomized yoke-controlled rt-fMRI NF experiment, with follow-up assessments at 3 and 6 months after rt-fMRI NF (Figure 2). Participants will be randomly assigned to the experimental group (NF/YC) and given random numbers by a third party, who encodes the intervention with matching random numbers. The experimenter who will rate the outcome and/or analyze the data will be blind to group assignment. The CRED-NF checklist indicating which analyses will be performed and listed as supplementary material (available on the Open Science Framework preregistration, https://osf.io/ec396; CRED-NF checklist, https://osf.io/8wcqt).

**Figure 2 F2:**
[figure not shown]
Consolidated Standards of Reporting Trials (CONSORT) flow diagram summarizing the study design.

#### Pre- and post-test

Before and after the neurofeedback intervention, the primary and secondary outcome measures of the depressive and anhedonic symptoms will be assessed in all subjects. The behavioral tasks will be repeated post-training to evaluate the NF training effect on goal-directed behavior. The follow-up assessments include the primary outcome of depression and secondary outcome of anhedonia, the goal-directed RL (model-based weighting parameter ω), and the CEN-SN functional connectivity (Pearson's correlation) based on prediction errors (PEs) (Figure 2).

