##### Computational modeling

MATLAB 2019a (https://www.mathworks.com/) and the Reinforcement Learning algorithm will be used to model the behavioral data and estimate the learning rate α, inverse temperature parameter β, repetition parameter p, and model-based learning weight ω of individual subjects.

① value estimates. The state-action values for the first and second stages of each trial are determined by the weighted sum of the model-based action value Q_MB_ and the model-free action value Q_MF._ The weighted sum is expressed as follows.

(1)
$$\begin{array}{l} Q_{net}\left(S_{A},a_{j}\right)=\omega Q_{MB}\left(S_{A},a_{j}\right)+{\left(1-\omega \right)Q}_{MF}\left(S_{A},a_{j}\right) \end{array}$$

It is assumed that individual behavioral choice in the first stage is the weighted sum of goal-directed and habitual learning, with the weight of ω (0~1). If ω is close to 0, the choice mainly depends on habitual learning; if ω is close to 1, the choice mainly depends on goal-directed learning.

(a) Model-based state-action value:

(2)
$$\begin{array}{l} Q_{MB}(S_{A},a_{j})=P(S_{B}|S_{A},a_{j})\underset{a\in \{a_{A},a_{B}\}}{\max}Q_{MF}(S_{B},a)\\ \;+P(S_{C}|S_{A},a_{j})\underset{a\in \{a_{A},a_{B}\}}{\max}Q_{MF}(S_{C},a) \end{array}$$

(b) Model-free state-action value:

(3)
$$\begin{array}{l} Q_{MF}\left(S_{i,t},a_{i,t}\right)=Q_{MF}\left(S_{i,t},a_{i,t}\right)+\alpha_{i}\delta_{i,t} \end{array}$$

For the first and second stages, learning rates α_1_ and α_2_, respectively, represent the extent to which the reward results are used for learning.

(c) Prediction error:

(4)
$$\begin{array}{l} \delta_{i,t}=r_{i,t}+Q_{MF}\left(S_{i+1,t},a_{i+1,t}\right)-Q_{MF}\left(S_{i,t},a_{i,t}\right) \end{array}$$

The action probabilities of the first and second stages of each trial are regarded as a softmax function of the inverse temperature parameter β, the repetition parameter *rep*, and the indicator function *p* as follows.

(5)
$$\begin{array}{l} P(a_{i,t}=a|s_{i,t})=\frac{exp(\beta [Q_{net}(s_{i,t},a)+p\cdot rep(a)])}{\sum_{a^{\prime }}exp(\beta_{i}[Q_{net}(s_{i,t},a^{\prime })+p\cdot rep(a^{\prime })])} \end{array}$$

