##### GD-RL behavioral and connectivity imaging indicators

The behavioral (model-based weighting parameter ω) and connectivity imaging indicators (CEN-SN activation difference) will be used as potential mediating factors to determine whether behavioral and imaging indicators could explain the changes in depressive and/or anhedonic symptoms. Within-group explorative analysis will be conducted using a stepwise regression using a bootstrapping test when multiple mediators are concerned (46) with PROCESS macro (http://www.afhayes.com/) of SPSS 22.

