## Discussion

The deficits in RL represent a sub-phenotype of anhedonia, with partially separable neural substrates (47). The decision-theoretic view of depression favors the compromise of the GD system, rather than the habitual system in depression (48), the former of which is present in both behavioral and neural manifestations during RL for clinical and subclinical depression (5, 7, 49). Acute stress affects the allocation of neural resources within large-scale brain networks, especially the balance between the CEN/SN in the GD system due to cognitive demands (50). Additionally, the acute stress (during the last month) is supposed to trigger shifts in goal-directed vs. habitual behavior pattern, which is concomitant with specific network configurations, especially frontostriatal circuits (CEN: LPFCal SN: VTA/putamen/caudate↓, lateral/medial OFC↓) (7). Stronger PEs may contribute to highly variable momentary mood fluctuations due to stronger reward feedback dynamics, whereas the influence of PEs on RL is compromised in depressed individuals (51). In summary, these studies highlight a promising target for RL-based NF interventions for anhedonic depression to produce flexible mood changes. Moreover, the focus on the GD-RL and imaging substrates in the current protocol may provide more insights with regard to the factors driving NF outcomes (38).

The novelty of the current study is that we focus on neither single ROI nor functional connectivity limited to a few ROIs, but rather the balance between two functionally intertwined brain networks (CEN/SN), and this approach has been utilized in self-regulation and sustained attention (27, 29). However, the impact of network-based NF on reward learning is still unknown. Thus, we propose to simultaneously decrease CEN and increase SN activity (CEN: LPFC↓; SN: VTA/putamen/caudate↑, lateral/medial OFC↑), which could potentially improve mood and its fluctuations. Individualized NF training based on a goal-directed subnetwork is potentially advantageous for improving treatment response to anhedonia symptoms for depressed patients.

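### At follow-up and in the mediation analysis goal-directed learning is represented only by ω, a share that also rises when habitual control weakens and goal-directed control does not change

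*Protocol article*

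**What the plan says.** All references are to the protocol article.

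- **Pre- and post-test.** The task is repeated after training with a stated purpose: "The behavioral tasks will be repeated post-training to evaluate the NF training effect on goal-directed behavior". That sentence names no parameter. The next one lists the follow-up assessments and identifies the behavioural measure as "the goal-directed RL (model-based weighting parameter ω".
- **Computational modeling.** Equation 1 makes the net first-stage value "the weighted sum of goal-directed and habitual learning, with the weight of ω (0~1". The section reads ω as a balance: "If ω is close to 0, the choice mainly depends on habitual learning", and near 1 the reverse. The parameters to be estimated include "inverse temperature parameter β, repetition parameter p, and model-based learning weight ω of individual subjects", so β is available separately from ω.
- **Behavioral data, Statistical analysis.** A mixed model measures the two systems separately. The transition × reward interaction stands for goal-directed learning, and "the main effect of reward feedback will represent the effect of the habitual system on the choice behavior (habitual RL". Its group factor is high-anhedonia patients against healthy controls.
- **GD-RL behavioral and connectivity imaging indicators.** "The behavioral (model-based weighting parameter ω) and connectivity imaging indicators" are the potential mediators of symptom change, in a within-group exploratory analysis.
- **Discussion.** The view of depression relied on "favors the compromise of the GD system, rather than the habitual system in depression".

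**The concern.** The second aim asks whether neurofeedback changes goal-directed learning in the short and long term. The rationale places the deficit in one system and not the other, and the patient-control analysis keeps the two apart. Yet at follow-up and in the mediation analysis the only behavioural quantity named is a ratio of the two.

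A ratio rises if its numerator grows or if the competing term shrinks. A training effect that merely weakened habitual responding would be reported as improved goal-directed learning, and a mediation result through ω would be described as working through the goal-directed system. At stake is the mechanistic conclusion of the second aim, not the clinical comparison.

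**Working it through.** The article states no figure on this point, so there is none to reproduce. The check is algebra on its equations, followed by an illustration.

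**Inputs from the article (Computational modeling)**
- Equation 1: Q_net = ω·Q_MB + (1−ω)·Q_MF.
- Equation 5: choice probability is a softmax of β·[Q_net + p·rep]. The text gives β1 to stage 1 and β2 to stage 2, so β is read as β1 for first-stage choice.

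**Step 1: substitute Equation 1 into Equation 5.** With Δ the difference between the two first-stage options, the choice logit is

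β1·ω·ΔQ_MB + β1·(1−ω)·ΔQ_MF + β1·p·Δrep.

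Hence:
- goal-directed weight β_MB = β1·ω
- habitual weight β_MF = β1·(1−ω)
- β_MB + β_MF = β1, and ω = β_MB/(β_MB + β_MF).

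**Step 2: put in illustrative weights.** These are assumptions; the article gives no values.

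| Change | β_MB | β_MF | β1 | ω |
|---|---|---|---|---|
| Start | 2 | 2 | 4 | 2/4 = 0.50 |
| Habitual weight halved only | 2 | 1 | 3 | 2/3 = 0.67 |
| Goal-directed −20%, habitual −60% | 1.6 | 0.8 | 2.4 | 1.6/2.4 = 0.67 |
| Goal-directed +50% only | 3 | 2 | 5 | 3/5 = 0.60 |
| Both +50% | 3 | 3 | 6 | 3/6 = 0.50 |

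In the second row ω rises although the goal-directed weight is unchanged. In the third it rises by the same amount although the goal-directed weight has fallen. In the last row the whole change goes into β1.

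**Step 3: size relative to between-patient spread.** Assume independent lognormal weights with median 2 and log-SD 0.5. Halving only β_MF moves mean ω from 0.50 to 0.65, about 0.95 of the baseline SD of ω. Over assumed log-SDs of 0.3 to 0.8 the shift runs from 1.58 down to 0.59 SD.

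**Step 4: does the article's own regression measure separate the systems?** The two-stage task was simulated with 70/30 transitions and reward probabilities drifting within 0.25–0.75. Assumed: 3000 agents of 200 trials, both learning rates 0.5, β2 = 4, p = 0.1, drift SD 0.025, starting weights 2.5 and 2.5. The first figure in each pair uses the update as printed in Equations 3–4; the second also passes the second-stage prediction error to stage 1.

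| Change | ω | Transition × reward (logit) | Reward main effect (logit) |
|---|---|---|---|
| Start | 0.500 | 0.88 / 0.83 | 0.03 / 1.08 |
| Habitual weight halved only | 0.667 | 0.89 / 0.87 | 0.02 / 0.57 |
| Goal-directed −20%, habitual −60% | 0.667 | 0.72 / 0.71 | 0.01 / 0.46 |
| Goal-directed +50% only | 0.600 | 1.24 / 1.22 | 0.02 / 1.07 |
| Both +50% | 0.500 | 1.19 / 1.17 | 0.06 / 1.59 |

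The interaction follows the goal-directed weight: nearly flat (+1% / +5%) when only habit falls, and down 18% / 14% when the goal-directed weight falls by 20%. ω goes up in both cases. The reward main effect follows the habitual weight only in the second variant; with the printed update it stays near zero.

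**The case against.** Several points against the concern are sound and limit it.

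- **A separable measure exists.** A reader might infer that the whole protocol measures goal-directed learning by ω alone. It does not: the mixed model under Behavioral data uses the transition × reward interaction. That model, however, has no factor for neurofeedback against yoked control and none for time, so as specified it does not answer the intervention question.
- **The post-test sentence names no parameter.** ω is fixed by name for follow-up and mediation only. The article also points to a preregistration and a checklist of analyses that are not shown, so its silence about other post-test analyses is not held against it.
- **An equal rise in both weights.** It is tempting to say that ω misses a real gain when both systems strengthen together. The documents do not support this. β is described as the randomness of choice, so a proportional rise in both weights is a rise in β1, and a flat ω is a fair description of an unchanged balance.
- **β1·ω has its own weakness.** It rises whenever choices become less random, for instance through practice on a repeated task. It cannot replace ω as a single measure.
- **Relative reliance is part of the article's framing.** The abstract says that depressed individuals depended less on goal-directed learning, and the modelling section defines ω correctly as a balance. If habitual control never moves, ω does track the goal-directed weight. Nothing in the article predicts that neurofeedback weakens habit selectively.
- **The analysis is exploratory**, and β can be recovered later.

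What remains is attribution. A rise in ω is compatible with either system having changed, and the plan as written would label it goal-directed. Recovering β later is possible, but choosing the quantity after seeing results would be post hoc.

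**Conclusion.** The point holds for follow-up and the exploratory mediation analysis. There ω is the only behavioural measure of goal-directed learning named, and by Equations 1 and 5 it is a share. A rise in it cannot by itself be attributed to the goal-directed system.

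The algebra rests on the printed equations alone. The sizes rest on assumed values: 0.50 to 0.67 when a habitual weight equal to the goal-directed one is halved, or roughly 0.6 to 1.6 baseline SDs over the spreads tried. They show what can happen, not what is expected.

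A reader might go further and conclude that the trial's efficacy result is compromised or that ω is an invalid parameter. Neither follows. HAMD-17 and SHAPS do not use ω, and ω is a legitimate index of balance. The consequence is confined to what the second aim can say about mechanism, but it is worth settling before data are seen.

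**What to change.** 1. Under Pre- and post-test, describe ω as the relative balance of goal-directed and habitual control, not as goal-directed learning itself.
2. From the same fit, report β_MB = β1·ω and β_MF = β1·(1−ω) beside ω for each patient and visit. In addition or instead, extend the mixed model under Behavioral data to arm (neurofeedback, yoked control) × time. If that model is relied on to show habit, check that its reward main effect responds to the habitual weight under the update rule actually fitted; in the simulation it did not under Equations 3–4 as printed.
3. State the reading rule in advance. Attribute a change to the goal-directed system only if β_MB (or the transition × reward interaction) changes and β_MF does not change by the same factor. Read a proportional change in both weights as choice consistency (β1), and a change in β_MF alone as habitual.
4. In the mediation analysis, show β_MB and β_MF as well as ω before calling the mediator goal-directed learning.

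**Cost.** No new data, scans or model are needed, and the article says recruitment had not begun at submission. The downside is a few more correlated and noisy estimates with 20 patients per arm, so the additional mediation results should stay descriptive.
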